**Table 2 T2:**
[figure not shown]
Schedule of enrollment, interventions, and assessment.

#### Safety assessment

2.6.3

Safety will be assessed by monitoring adverse events. Any adverse events or abnormalities that may occur in this study, including bleeding, local hematoma, infection, pallor, sweating or dizziness, fainting during acupuncture treatment, and objective worsening of existing symptoms, will be voluntarily reported and documented on case report forms (CRFs). The CRFs will record the adverse events in detail, including the time and date of occurrence, degree of severity, any measurement related to the treatment of the event, and any potentially causal relationship between the treatment and the event. If any severe adverse event occurs, acupuncture intervention will be ceased immediately, and the principal investigator will be informed and will take proper actions. It is required to report the events and actions that have occurred to the ethics committee of the hospital.

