### Trial design and setting

2.1

This study is a single-center, outcome-assessor, and statistician-blinded, randomized, and controlled trial that was devised according to the Standards for Reporting Interventions in Clinical Trials of Acupuncture.^[24]^ The study consists of 4 stages: enrollment, allocation, intervention, and analysis. Each participant will be registered only once. The total study period for this trial will be 12 months (follow-up to 12 months after injury), including a 1-month treatment phase. This is the initial version of the protocol. The start of this study will been plan on January 10, 2022, and ends on June 10, 2024. It may be completed ahead of schedule if a sufficient number of patients are recruited.

The study will be carried out in the Neurosurgery Center of Qionghai People's Hospital, Hainan Province, China, and all participants will be recruited from the inpatients in this center. A minimum of 40 patients who meet the eligibility criteria and sign an informed consent form are expected in this hospital each year. Patients with TBI (GCS score of 6∼12 and brain edema on CT scan) will be divided into 2 groups; the control group will receive conventional treatment, and the study group will receive additional acupuncture as an adjuvant therapy, once a day for 28 days, starting within 72 hours after the injury.

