#### Eligibility criteria: inclusion criteria

2.3.1

Adults with TBI who fulfill the following inclusion criteria are eligible: an initial GCS score between 6 and 12 on admission; one or more brain contusions with visible pericontusional edema on the CT scan; age between 16 and 75 years; agreement to undergo acupuncture treatment within 72 hours after injury or craniotomy; and completion of informed consent by a legal representative.

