### Randomization and blinding

2.4

To ensure a balanced sample size across groups over time, the study is using stratified block randomization in a 1:1 ratio that divides patients into 2 groups according to the GCS (scores of 6∼8 or 9∼12). The study will also apply block randomization method with a block size of 2 (post-craniotomy or no craniotomy).

Random numbers will be made by a computerized number generator list provided by a statistician not involved in the determination of eligibility or in the assessment of outcomes. The allocation of participants will be sealed in sequentially numbered, opaque envelopes.

After verification that a patient meets all the inclusion criteria and none of the exclusion criteria, and after the informed consent is signed by legal representative, the doctor responsible for the patient will assign a correlative number to the patient who will be allocated to either the study group or the control group.

The blinding of this study is limited because it is easily discernible that some patients are receiving acupuncture therapy, and the acupuncturist cannot be blinded. However, the outcome assessors and statistician will be blinded and unaware of patient allocation. During the whole research process, unblinding will be carried out after the statistical analysis is completed.

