#### Interventions

2.5.1

In addition to conventional treatment, patients in the study group will receive acupuncture as adjuvant therapy, which will start within 72 hours after injury or craniotomy; acupuncture will be administered once a day for 28days (a total of 24 treatments with 1 break per week). All interventions will be performed by the same acupuncturist doctor, who has more than 10 years of clinical experience and who will be trained in the study protocol before the start of the trial. Encouragement and supervision from acupuncturists can help improve participants’ adherence.

Only sterile, stainless, disposable acupuncture needles (size: from 0.25 × 30 mm to 0.25 × 50 mm; Suzhou Hwato Acupuncture Medical Appliance Company, China; product no. 20162270970) will be used. In the study group, acupuncture needles will be inserted into acupuncture points located on the midline of the human body (GV20, GV26, and CV9) and on the affected limbs (GB20, GB39, PC6, LI4, ST36, ST40, SP6, KI7, and LR3). If the GV20 point is too close to the surgical site, this acupoint may be skipped. All the acupoints have been selected and localized according to the guideline of WHO Standardized Acupuncture Point Location, and then depending on where the needle is located the insertion depth will be 10 to 40 mm.^[25]^ The needles will be manipulated using twirling, lifting, and thrusting methods to promote Qi. Because patients are not able to express their feelings, eye moisture or the presence of tears will be considered as a kind of Deqi. After insertion, needles will be left in position for 30 minutes in every session and the manipulations of twirling, lifting, and thrusting will be repeated for 1 minute/10 minutes. The location of the relevant acupoints is summarized in Table 1.

**Table 1 T1:** Description of the location of the applied acupoints.

Acupoints	Descriptions
Baihui (GV20)	Straight up 5 cun above the middle of the front hairline
Shuigou (GV26)	At the junction of the upper and middle third of the philtrum
Fengchi (GB20)	Below the occiput, the depression between the upper end of the trapezius muscle and the upper end of the sternocleidomastoid muscle.
Xuanzhong (GB39)	On the outside of the calf, 3 cun above the tip of the lateral malleolus, and the depression of the front edge of the fibula
Shuifen (CV9)	On the upper abdomen, anterior midline, 1 cun above the middle of the umbilicus

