### Statistical analysis

2.10

After a patient has been randomly assigned, the outcome measures will be collected even if the trial treatment is interrupted or not given. The data used will include the method of the last observation carried forward or the method of the worst observation carried forward.^[26]^ That is, this study will analyze the data with the full analysis set.

The statistical analyses will be performed by a blinded researcher. According to the intention-to-treat principle, all the data will be analyzed using the SPSS statistical software package (version 20.0, IBM SPSS Statistics, IBM Corp, Somers, NY). Baseline characteristics will be described and compared. Continuous variables subject to normal distribution will be presented as the mean ± standard deviation; continuous variables not subject to normal distribution will be expressed as the median and interquartile range; and categorical variables will be described as the frequency and percentage.

GOS, wake-promoting rates, and adverse events rates will be compared using the chi-squared or Fisher's exact tests. GCS and MBI scores will be compared between the 2 groups by *t* test with a 95% confidence interval. The results of the volume of TBE and the serum levels of CRP and IL-6 between the 2 groups will be compared using either a generalized linear mixed model or the *t* test, and repeated contrast tests will be conducted to account for time differences in each group. If the data are not normally distributed, nonparametric methods will be used. For all analyses, the results with a *P* value less than .05 will be considered statistically significant. The clinical efficacy should be determined in the evaluation of clinical significance.

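### Adverse events are captured by voluntary reporting while only the study arm has 24 additional sessions with an unblinded acupuncturist, so the planned between-arm comparison of event rates may mix detection with harm

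*Protocol article*

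**What the plan says.** The provisions that bear on this point, all from the protocol article, are these.

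- **Capture (2.6.3 Safety assessment).** Adverse events or abnormalities "will be voluntarily reported and documented on case report forms (CRFs"). The section names no reporter and gives no timetable of enquiry. Its list runs from bleeding and infection to pallor, sweating and dizziness, and includes "fainting during acupuncture treatment".
- **Population (2.3.1).** Patients have "an initial GCS score between 6 and 12 on admission".
- **Ability to speak for themselves (2.5.1 Interventions).** In describing how the needling response is recognised, the text says: "Because patients are not able to express their feelings".
- **Contact in the study arm (2.5.1).** Acupuncture runs over 28 days, "a total of 24 treatments with 1 break per week", with needles left in for 30 minutes at each session. Section 2.4 adds that "the acupuncturist cannot be blinded".
- **Contact in the control arm (2.1).** "the control group will receive conventional treatment, and the study group will receive additional acupuncture as an adjuvant therapy". No sham or matched contact is described.
- **Analysis (2.10).** "adverse events rates will be compared using the chi-squared" or Fisher's exact test, and the 0.05 threshold applies to every analysis.

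Some provisions apply to both arms: data taken from routine medical records (2.8), investigator inspection of treatments (2.5.2), assessments at days 7, 14 and 28 (2.6.2), and monthly follow-up contacts after the four treatment weeks (2.7).

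**The concern.** An observed event rate is the true rate multiplied by the share of events that someone notices and records. A between-arm test says something about harm only if that share is about the same in both arms. Here capture is described as voluntary, and many patients will be unable to report for themselves, at least early on. Reports therefore depend on who is at the bedside. In the study arm that includes a practitioner at 24 sessions who knows the allocation; the control arm has no counterpart.

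The article's abstract makes safety one of the two aims. If detection differs by arm, a spurious excess could be declared, or a real excess put down to closer observation. A later analysis plan cannot repair this, because events that were not sought during treatment cannot be recovered at analysis.

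**Working it through.** **Number of additional contacts.** 28 days less one break in each of 4 weeks is 28 − 4 = 24 sessions, which reproduces the protocol's figure. The matching number in the control arm is 0.

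**Inputs from the document.** 40 patients per arm (2.9); chi-squared or Fisher's exact test, threshold 0.05 (2.10).

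**Inputs assumed, because the document gives none.** The same true risk p in both arms, at 20%, 40% or 60%. Detection share s₁ = 95% in the study arm; s₀ = 60% or 85% in the control arm.

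**Formulas.** Observed rate in arm j = p × sⱼ. The false-positive rate is the sum, over all pairs (a, b) from 0 to 40, of Bin(a; 40, p·s₁) × Bin(b; 40, p·s₀), counting only pairs for which the test gives P < 0.05. Both tests are two-sided and the chi-squared is uncorrected. For example, at p = 40% the observed rates are 0.40 × 0.95 = 38% and 0.40 × 0.60 = 24%.

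| True risk, both arms | Detection, study v control | Observed, study v control | Chi-squared | Fisher |
|---|---|---|---|---|
| 20% | 95% v 60% | 19% v 12% | 14% | 9% |
| 40% | 95% v 60% | 38% v 24% | 27% | 20% |
| 60% | 95% v 60% | 57% v 36% | 49% | 40% |
| 20% | 95% v 85% | 19% v 17% | 5.8% | 3.2% |
| 40% | 95% v 85% | 38% v 34% | 6.5% | 4.0% |
| 60% | 95% v 85% | 57% v 51% | 9.2% | 5.8% |

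With equal, complete detection at the same true risks, the rates are about 5% for chi-squared and about 3% for Fisher. The arms are of equal size, so exchanging the two detection shares leaves every rejection probability unchanged but makes the spurious excess appear in the control arm.

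**A wider range.** With study-arm detection of 90%, control-arm detection of 30% to 70% and true risk of 10% to 50%, the false-positive rate runs from 7.1% to 85.2% (chi-squared) and from 1.6% to 79.3% (Fisher). The low end is a true risk of 10% with 90% v 70% detection, where the effect is small.

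**Events that only needling can cause.** Suppose a 20% background risk in both arms and, independently, needling events in 15% of study patients. The study-arm rate for any event is then 1 − 0.80 × 0.85 = 32%, against 20%. Chi-squared is significant in 23% of such trials. That difference is real harm, so 23% is the power to detect it and not a false-positive rate.

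**The case against.** The strongest reply is that controls are far from unobserved. All participants are recruited as neurosurgical inpatients; study data come from routine records in both arms; investigators inspect treatments and record changes; and both arms share the day 7, 14 and 28 assessments and the monthly contacts. Most listed events are visible signs that do not depend on the patient speaking, and the sentence about patients not expressing their feelings concerns the needling response, not adverse event reporting. Table 2, the assessment schedule, is not visible in the text at hand and may list adverse event checks.

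Much of this stands. A reader might infer that only the study arm is watched; the document does not support that. The 24 sessions are additional contact, and the gap is probably small for serious events that reach the routine record. What remains is that none of the provisions shown sets equal active enquiry for adverse events during the 28 days. Treatment inspection concerns treatments, and the monthly contacts begin after needling has ended. If Table 2 does schedule checks, the wording of 2.6.3 needs to agree with it.

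A reader might also infer that an event possible only with needling, such as fainting at a session, biases the comparison and should be left out of the test. That does not follow. Such an event is a harm of the intervention and belongs in a comparison of the arms as randomised; removing it could hide harm.

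Finally, a reader might infer that the error must run against acupuncture. More contact would tend to raise the study-arm count, but an unblinded acupuncturist reporting voluntarily could also under-report. The document does not settle the direction.

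**Conclusion.** The concern holds in a limited form. Section 2.6.3 makes capture voluntary, contact differs by arm during treatment, and 2.10 tests the resulting rates against each other, so the comparison may mix detection with harm. The problem is greatest for minor or transient events such as pallor, sweating or dizziness.

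Its size depends on detection shares and event rates that the document does not give. A large detection gap (95% v 60%) would raise the false-positive rate several-fold under either test; a small one (95% v 85%) would barely move it. The choice between chi-squared and Fisher changes the level but does not remove the problem. This is a secondary comparison and the sample size is unaffected, but the change is worth making before recruitment because it cannot be made afterwards.

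**What to change.** **In 2.6.3**, replace voluntary reporting with one solicited adverse event checklist, identical in both arms. It should be completed at the existing day 7, 14 and 28 assessments and at the monthly contacts, by existing ward or follow-up staff other than the acupuncturist. Make the text and Table 2 agree.

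**In 2.10**, keep the between-arm comparison of all adverse events. Add a descriptive table of needling-related events for the study arm only, per patient and per session.

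**Cost.** One case report form page and a few sentences of text; no new visits, no change to treatment and no change to the sample size. The small downside is that more control-arm events will be recorded.

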### Follow-up

2.7

After 4 weeks of complement acupuncture treatment, the trial will enter a follow-up period till 12 months after injury, when all participants receive the equal therapy as possible follow-up on a monthly basis via telephonic and message communications or outpatient review, treatment compliance and changes of clinical manifestations will be faithfully recorded. The data of 6-month and 12-month will be used for the final statistical analysis of the trial.

### Data collection

2.8

Participants’ identification records will be kept confidential until the results of the study are published. All the study data will be collected from the patients’ routine medical records by the investigator and registered on the CRFs. The information on CRFs will then be entered into a predesigned, password-protected electronic data set by 2 independent investigators who will be blinded to group allocation. To ensure accuracy, any corrections made to the CRFs must be personally signed and dated by the person responsible, and another researcher will double-check the entered data. Original paper CRFs will remain at the trial site. The data will be used in accordance with local law and ethics committee approval. The original data will be shared through ResMan, which is the Clinical Trial Management Public Platform (http://www.medresman.org.cn/uc/index.aspx).

The Data and Safety Monitoring Board (DSMB) for this study will supervise the entire process. All members of the DSMB are independent of the study sponsor and have no competing interests.

### Sample size calculation

2.9

Because the data available for patients with TBE who receive early acupuncture treatment are limited and inconclusive, we will perform a single-blind RCT in which the control group will receive conventional treatment and the study group will receive additional acupuncture as an adjuvant therapy. The primary outcome will be dichotomized GOS (poor recovery = GOS 1∼3; good recovery = GOS 4∼5) at 6 and 12 months of follow-up after the injury. According to our previous pilot study, the change of GOS (good recovery rate) in the study group was shown to be 80% (n = 12), and that in control group was 50% (n = 12). Sample size was calculated using the Power Analysis and Sample Size (PASS) software package (version 15, NCSS, Kaysville, UT), with a 2-sided significance level (α = 0.05), a power of 80%, and chi-squared tests to assess the difference in rates between the 2 groups. Thus, a total sample size of 80 participants (40 per group) will be recruited, allowing for 10% loss during follow-up.

### Statistical analysis

2.10

After a patient has been randomly assigned, the outcome measures will be collected even if the trial treatment is interrupted or not given. The data used will include the method of the last observation carried forward or the method of the worst observation carried forward.^[26]^ That is, this study will analyze the data with the full analysis set.

The statistical analyses will be performed by a blinded researcher. According to the intention-to-treat principle, all the data will be analyzed using the SPSS statistical software package (version 20.0, IBM SPSS Statistics, IBM Corp, Somers, NY). Baseline characteristics will be described and compared. Continuous variables subject to normal distribution will be presented as the mean ± standard deviation; continuous variables not subject to normal distribution will be expressed as the median and interquartile range; and categorical variables will be described as the frequency and percentage.

GOS, wake-promoting rates, and adverse events rates will be compared using the chi-squared or Fisher's exact tests. GCS and MBI scores will be compared between the 2 groups by *t* test with a 95% confidence interval. The results of the volume of TBE and the serum levels of CRP and IL-6 between the 2 groups will be compared using either a generalized linear mixed model or the *t* test, and repeated contrast tests will be conducted to account for time differences in each group. If the data are not normally distributed, nonparametric methods will be used. For all analyses, the results with a *P* value less than .05 will be considered statistically significant. The clinical efficacy should be determined in the evaluation of clinical significance.

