## Introduction

1

Traumatic brain edema (TBE) is defined as a pathological condition in which the fluid content in the brain tissue increases abnormally and the brain volume increases after traumatic brain injury (TBI) or craniotomy; TBE commonly manifests as pericontusional edema after brain contusions.^[1]^ Localized cerebral edema, erupting simultaneously with brain contusions, might lead to increased intracranial pressure (ICP), cerebral herniation, and ultimately death.^[2]^ TBE, an independent prognostic variable of all severe TBI, is the most common and serious complication of TBI. TBE contributes to approximately 50% of the deaths of patients with severe TBI.^[3]^ In China, 53.17% of patients experience unfavorable outcomes from TBI, which include severe disability, a vegetative state, and death.^[4]^ As medicine has advanced rapidly, the survival of patients with TBI has also improved in recent years. However, the long-term treatments needed for the survivor place inconveniences and financial pressures on the family and society.^[5]^

TBE is a major cause of death and severe, prolonged disability in patients with TBI. Research on the treatment and the prevention of TBE has continued for more than half a century, but there has been no breakthrough in this field. Evidence from evidence-based medicine have shown that only few other treatments have definite efficacy for TBE beyond craniotomy and mannitol.^[6]^ However, craniotomy and mannitol treatment have limitations. For example, brain edema may progress after craniotomy, and mannitol may cause adverse effects that include ICP rebound and kidney damage.^[7]^

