#### Secondary outcomes

2.6.2

The secondary outcomes are wake-promoting rates, changes in the GCS (Baseline GCS is used as the basis for grouping), the volume of TBE calculated by CT scan (i.e., the volume of brain contusions and pericontusional edema), and the serum levels of CRP and IL-6 measured at four different time points (baseline and days 7, 14, and 28 after treatment). Another secondary outcome, the Modified Barthel Index (MBI), will be measured at the beginning of treatment, at the end of 28-day treatment, at the 6-month and 12-month follow-up after injury.

Calculating the volume of TBE, including the volume of brain contusions and pericontusional edema, by CT scan with the help of 3D Slicer software (version 4.8.1) might reduce the subjective impact of quantifying brain edema. 3D Slicer is a free, open source, and multi-platform software package widely used for medical, biomedical, and related imaging research; it has been jointly developed by multiple institutions and has been supported by the National Institutes of Health in the United States.

The Human IL-6 ELISA kit (Wuhan Fine Biotech Co., Ltd., China) or the Human C-Reactive Protein ELISA kit (Head Office in China Beckman Coulter Commercial Enterprise (China) Co., Ltd. Shanghai, China) will be used to determine the concentrations of IL-6 or CRP in the samples, and the data will be analyzed. Collected samples will be centrifuged for 15 minutes at 1000 × *g* and stored in a freezer at −80 C until they are ready for processing and analysis. Samples will be discarded after the analysis. The timepoints for assessment are listed in Table 2.

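### The carry-forward rule in section 2.10 has no exception for death, so as written it enters pre-death values on the secondary outcomes for patients who have died

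*Protocol article*

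**What the plan says.** Section 2.10 (Statistical analysis) states one rule for incomplete data: "The data used will include the method of the last observation carried forward or the method of the worst observation carried forward". The next sentence ties it to the analysis population: "this study will analyze the data with the full analysis set". The paragraph after that invokes intention to treat: "According to the intention-to-treat principle, all the data will be analyzed using the SPSS statistical software package". No outcome is singled out, the choice between last and worst is left open, and death is not mentioned.

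The tests are given in the same section. For the two scores: "GCS and MBI scores will be compared between the 2 groups by *t* test with a 95% confidence interval". CT oedema volume, CRP and IL-6 "will be compared using either a generalized linear mixed model or the *t* test". Nonparametric methods are allowed where data are not normal.

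Section 2.6.2 has GCS, volume, CRP and IL-6 "measured at four different time points (baseline and days 7, 14, and 28 after treatment". MBI is taken at the start, at day 28, and at 6 and 12 months.

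Deaths are to be expected. The Introduction says "TBE contributes to approximately 50% of the deaths of patients with severe TBI", and the Discussion describes traumatic brain oedema as the leading cause of death after such injury. Entry requires GCS 6 to 12 with visible oedema. No mortality figure for this population is given.

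**The concern.** Last and worst observation carried forward both insert a value that was observed, and for a patient who has died every observed value predates death. GOS has a place for death, in its poor category (1 to 3). GCS, MBI, volume, CRP and IL-6 have none.

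Three cases show the effect of the literal rule:

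- A patient at GCS 6 on day 7 who dies on day 10 is entered as 6 on days 14 and 28 under last, and also under worst if 6 was the lowest score.
- A patient who dies before day 7 with only a baseline scan is entered with zero oedema growth at every later time point, under either option.
- A patient who dies in month 4 is entered, under last, with the day-28 MBI at 6 and 12 months.

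Two things are at stake. A survival difference between arms is diluted on GCS and MBI. The volume comparison, which answers an aim stated in the Introduction and Discussion, is shifted by deaths rather than by oedema.

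**Working it through.** **The plan's own figure.** The only computed figure is the sample size, 40 per group. The unpooled formula for 50% vs 80% gives (1.960 + 0.842)² × (0.25 + 0.16) / 0.30² = 35.8, so 36 per arm, and 36 / 0.90 = 40. It rests on GOS, where death has a category, so this point leaves it untouched. It is used below only as the arm size in a simulation.

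**Inputs.** From the document: the carry-forward rule, the tests, the time points, the baseline GCS range of 6 to 12, and 40 per arm. Assumed: every death rate, survivor mean, carried value and SD.

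**GCS.** Arm mean = (1 − m) × 13 + m × v, where m is 28-day mortality (10% vs 20%), 13 is the survivors' mean and v is the value entered for a death.

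| v | 10% arm | 20% arm | Difference |
|---|---|---|---|
| 3 (death scored at floor) | 12.0 | 11.0 | 1.0 |
| 5 carried | 12.2 | 11.4 | 0.8 |
| 6 carried | 12.3 | 11.6 | 0.7 |
| 8 carried | 12.5 | 12.0 | 0.5 |

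So 20% to 50% of the difference is lost. With deaths of 10% vs 30%, the difference is 0.20 × (13 − v): 2.0 at v = 3, 1.4 at v = 6 and 0.2 at v = 12.

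**MBI.** With survivors at 60 and deaths of 10% vs 30%, the difference is 0.20 × (60 − c), where c is the carried score. It is 12 if c = 0, the same as scoring death at 0, and 8 if c = 20. A carried value near 0 does almost no harm.

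**CT volume, no treatment effect in survivors.** Mean change per arm = (1 − d) × g + d × c, where d is early deaths (5% vs 15%), g is survivors' change and c is the carried change.

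- Baseline carried (c = 0): the arm with more deaths looks better by 0.10 × g, which is 0.5, 1 or 2 mL for g = 5, 10 or 20 mL. At g = 10 the means are 9.5 and 8.5 mL.
- An interim scan carried (c = 5, g = 10): 9.75 vs 9.25 mL, so 0.5 mL.
- Survivors shrinking (g = −10, c = 0): −9.5 vs −8.5 mL, so the arm with more deaths looks 1.0 mL worse.

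**Effect on the t test.** A simulation used 40 per arm, survivors' growth 10 mL, SD 10 mL, baseline carried and 5,000 runs. The test significantly favoured the arm with more deaths in 6.7% of trials (deaths 5% vs 15%) and 14.5% (10% vs 30%), against a nominal 2.5%. With equal deaths of 10% it was 2.2%. With survivors shrinking by 10 mL, the excess fell on the other side: 6.9% and 14.9% against the arm with more deaths.

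**The case against.** The strongest reply is that nothing says deaths are carried forward. The rule follows a sentence about collecting outcomes when treatment is interrupted or not given, so discontinuation is its natural setting, and a condensed article may leave death to a fuller plan. It is true that the application to deaths is an inference. But the rule is general, is tied to the full analysis set under intention to treat, and has no exception. The point is therefore what a stated rule produces, not a missing detail.

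Other objections stand and limit the point:

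- The wake-promoting rate uses all patients in the group as its denominator, so a patient who dies without reaching GCS 15 is already a failure.
- A mixed model fitted to observed values would not carry volume, CRP or IL-6 forward. Section 2.10 equally permits a t test, so the problem is possible there, not certain.
- Data come from routine records, so an interim scan or a late GCS might be the value carried, which reduces the distortion.
- The exclusion for unstable vital signs within 72 hours should remove some early deaths.
- GCS 3 for death is a convention, since a living patient can also score 3. The 1.0-point reference difference depends on it.

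A reader might infer that the arm with more deaths will look better on oedema. The document does not support that: the direction depends on whether survivors' volume is above or below the carried value. A reader might also take the 50% in the Introduction, or the 50% good recovery assumed for controls, as a mortality rate. The first is oedema's share of deaths in severe injury. The second leaves a poor category that also includes severe disability and vegetative state.

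**Conclusion.** The point holds for secondary outcomes. Taken as written, section 2.10 enters pre-death values for patients who have died in the GCS and MBI comparisons, and in the volume and biomarker comparisons if these are t tests on carried-forward data. Selecting worst instead of last does not remove the problem, except nearly so for MBI when the starting score is close to 0.

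Under the assumptions above, a survival difference worth 1.0 GCS point is reported as 0.8 to 0.5, and the volume comparison moves by 0.5 to 2 mL in a direction set by survivors' course. The sizes scale with the difference in deaths between arms, about which the document gives nothing. If deaths are few or balanced, the between-arm effect is small.

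The primary GOS result and the sample size are not in question.

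**What to change.** Add one paragraph to section 2.10:

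- No observation is carried forward past the date of death.
- GCS and MBI: from the date of death enter the floor score (3 and 0), state that this is a convention, and compare the arms by a rank-based test, which the section already allows.
- CT volume, CRP and IL-6: analyse values observed while alive, for example by the mixed model already named, and report deaths by arm at each time point beside the result. That model still treats values after death as missing, which is why the death counts must be shown with it.
- As a sensitivity analysis only, repeat the volume and biomarker comparisons with deaths ranked worst. As the main analysis this would turn mechanistic outcomes into partial mortality composites and give no difference in mL or concentration.

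The cost is a paragraph of text. No new measurement is needed, since the monthly follow-up in section 2.7 should supply dates of death. The downside is small: the GCS and MBI results become partly mortality composites, and the volume and biomarker results are conditional on being alive.
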